
### Qualitative data collection

Following completion of the 6-month surveys at the intervention sites, focus group discussions and key informant interviews will be conducted at four organizational levels (i.e., patient, provider, management, policy) for an in-depth understanding of contextual factors influencing the implementation outcomes of interest. At least one patient focus group and three key informant interviews representing providers and managers will be conducted at each study site with 1 to 2 key informant interviews relevant to the district or the Central Region. The target numbers of participants indicated are estimates; the actual numbers for each study site will be determined when saturation is reached [66]. Interviews will be conducted by trained research assistants supervised by the researchers. We will use a semi-structured interview guide [67] to conduct 60-min audio-recorded interviews.

### Statistical analysis plan

Data will be cleaned and reviewed to determine if distributional assumptions are met. If not, scores will be transformed, or appropriate nonparametric methods will be applied. If distributional assumptions are valid, sensitivity analyses (with and without outliers) will be applied. Hypothesis testing will use α = 0.05 (2-tailed). An intent-to-treat analysis will be used to maintain baseline comparability achieved by randomization.

#### Quantitative data analysis

Descriptive analysis will be used for implementation outcomes scores at each health facility; scores will be compared within health facilities and between study arms over time. Mixed models (Linear Mixed Models or Generalized Linear Mixed Models) will account for repeated participant measures.*For Likert scale items (surveys)*, we will use ANOVA to determine differences in implementation outcome scores between study arms, with Tukey HSD (honestly significant difference) post hoc analysis to determine specific sites that significantly differ.*For continuous outcome variables*, we will similarly use linear mixed models to analyze treatment effects while controlling covariates, including age, education, income, religion, marital status, employment, insurance, and clinical conditions consistent with our previous studies [68, 69].*Fidelity analysis:* The fidelity checklist and activity log sheets at each study site will be aggregated, and composite site scores will be calculated and compared across intervention and control sites.*Cost-Effectiveness Analysis:* Costs will be determined using the cost trackers described. At the facility level, we will use the WHO Incremental Cost-Effectiveness Ratio (ICER) [70]. A formula to analyze the cost-effectiveness outcome, whose outcome of interest is screening and treatment. An ICER is calculated by dividing the difference in total costs (incremental cost) by the difference in the chosen measure of health outcome or effect (incremental effect) to provide a ratio of ‘extra cost per extra unit of health effect. We will determine the Total Cost [average fixed and variable costs (TC)] for screening and treatment in IG (Arm 1) and CG (Arm 2), and cervical cancer cases averted (incremental effect) for each Arm. Then ICER = Incremental cost/Incremental effect. An ICER of less than 1 indicates that the control group is cost-effective, an ICER greater than 1 suggests the intervention group is cost-effective, and an ICER equal to 1 indicates a similar cost for both arms. At the patient level, we will calculate the average cost per patient in both arms.

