#### Sample size estimation

The sample size is calculated based on implementation outcomes of health system adoption, cost, fidelity, penetration, and sustainability.*For power calculation*, we used Power (1 − β) = 0.8 and α = 0.05 and did not assume equal cluster sizes. The coefficient of variation (CV) of cluster sizes is set to 0.2, allowing for a large variability between clusters. Methods from Donner et al. [59] implemented in R for cluster RCTs were used.*For binary outcomes**,* e.g., adoption, we assumed 15% adoption in the control group based on previous study [23]. Table 3 shows the sample size needed to detect increases in implementation outcomes (e.g., adoption) in the intervention arm from 15% to 25–50% with 80% power. We expect to achieve an increase of at least 15%, to 30% or more, for outcomes such as adoption.*For continuous outcomes* such as sustainability/sustainment, we used estimated variance = 1 (standardized), and variance within clusters = 0.95 (assuming a large proportion of individual WLWH variability). For average cluster sizes (sampling frame per facility) ranging from 400 to 600 WLWH, we have greater than 80% power to detect differences in mean scores between the intervention and control arms as small as 1.4. We aim to recruit at least 1,152 patients (288 per site × 4 sites, inclusive of 20% attrition for a minimum sample size of 240 per site) Thus, the sample size for the Intervention Arm is *n* = 576 and Control Arm is *n* = 576.

**Table 3 Tab3:** Power and sample size calculation

Intervention Numeric	Control Numeric	Minimum Sample Size Per Site
0.25	0.15	504
0.30	0.15	240
0.35	0.15	142
0.40	0.15	94
0.45	0.15	67
0.50	0.15	50

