### Randomization

Study sites are the unit of randomization, and all providers and WLWH at a given HIV clinic at each site will be randomized to the same study arm. Using computer-generated numbers with a block of 2, the four study sites will be randomized to one of two arms: two sites in the intervention group and two sites in the control group (Fig. 3).

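### Apart from fidelity, no stated between-arm analysis accounts for the clinic, which is the randomised unit, so the two-sided 5% level is not protected once clinics differ

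*Protocol article*

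**What the plan says.** - Randomization: "Study sites are the unit of randomization", with "two sites in the intervention group and two sites in the control group".
- Sample size estimation plans with cluster-trial methods: "we used Power (1 − β) = 0.8 and α = 0.05 and did not assume equal cluster sizes", and "The coefficient of variation (CV) of cluster sizes is set to 0.2". For continuous outcomes it sets total variance 1 and within-cluster variance 0.95, so correlation within a clinic is assumed.
- Quantitative data analysis gives mixed models one stated purpose: "Mixed models (Linear Mixed Models or Generalized Linear Mixed Models) will account for repeated participant measures". Continuous outcomes are likewise given linear mixed models, with individual covariates and no named clinic term.
- For Likert survey items: "we will use ANOVA to determine differences in implementation outcome scores between study arms, with Tukey HSD" as a follow-up to find which sites differ.
- Fidelity is the exception. Checklists and logs are aggregated to a composite per site, and these composites are compared between arms.
- Statistical analysis plan sets a two-sided 5% level for hypothesis tests.
- The Analysis paragraph of the Sustainment phase carries the same methods forward.
- Outcomes measures makes screening uptake a primary outcome, scored as complete or not for each enrolled woman.

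**The concern.** When whole clinics are allocated, the arm effect has to be judged against variation between clinics. ANOVA on individual scores judges it against variation between people, and this remains so if the sites are entered as groups for the Tukey comparisons. A random effect for the participant handles several measurements on one woman but not the similarity of women within a clinic. For an outcome recorded once per woman, such as uptake, it adds nothing.

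Planning therefore assumes clinic correlation for continuous outcomes, while the stated person-level analyses do not use it. With only two clinics per arm, ordinary differences between hospitals can then be reported as an effect of the implementation support strategies, at an error rate above the stated 5%.

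**Working it through.** **Inputs.** Two sites per arm (Randomization). Two-sided α 0.05 (Statistical analysis plan). 240 women per site after attrition, CV of cluster size 0.2, and 15% versus 30% (Sample size estimation). 80 providers (Abstract), so 80/4 = 20 per site if evenly spread; the even spread is an assumption. ICC for continuous outcomes = 1 − 0.95 = 0.05. No ICC is given for binary outcomes or provider scores, so a range is used.

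**The plan's own figures.** Table 3 gives 240 per site for 30% versus 15%. A noncentral t on 2 df with unpooled binomial variance and ICC 0 has noncentrality 0.15/√[(0.30×0.70 + 0.15×0.85)/(2×240)] = 0.15/√(0.3375/480) = 5.66 and power 80.0%. Solving the same formula for each row returns 504, 240, 142, 94, 67 and 50, which matches all six rows. Other inputs also fit: the unpooled size per arm times a design effect of 2.038, which 500 per cluster, ICC 0.002 and CV 0.2 would give. The ICC behind the table is therefore inferred, not stated. For continuous outcomes, a difference of 1.4 with ICC 0.05, 400 to 600 per site and 2 df gives power of about 84% to 85%, consistent with the claim of more than 80%.

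**Type I error if the clinic is left out.** Design effect DE = 1 + (m − 1)×ICC; type I error = 2×[1 − Φ(1.96/√DE)].

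| ICC | Women, m = 240: DE | Type I error | Providers, m = 20: DE | Type I error |
|---|---|---|---|---|
| 0 | 1.00 | 5% | 1.00 | 5% |
| 0.002 | 1.478 | 10.7% | 1.038 | 5.4% |
| 0.01 | 3.39 | 28.7% | 1.19 | 7.2% |
| 0.02 | 5.78 | 41.5% | 1.38 | 9.5% |
| 0.05 | 12.95 | 58.6% | 1.95 | 16.0% |

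Allowing for the CV of 0.2, DE = 1 + (1.04m − 1)×ICC. At ICC 0.05 this is 13.43 for women (59.3%) and 1.99 for providers (16.5%). With 10 providers per site and equal sizes, the ICC 0.05 figure is 10.4%.

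Simulation under the null (40,000 runs, two sites per arm, individual-level ANOVA) gives 59.3%, 29.4% and 10.9% for 240 women at ICC 0.05, 0.01 and 0.002. For 20 providers it gives 16.2%, 7.4% and 5.5%. In the same runs, a t test on the four site means with 2 df rejects 4.9% to 5.2% of the time.

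**Power of the 2-df analysis, 15% versus 30%, 240 per site.** Noncentrality = 0.15/√(0.3375×DE/480).

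| ICC | Noncentrality | Power |
|---|---|---|
| 0 | 5.66 | 80% |
| 0.002 | 4.65 | 67% |
| 0.01 | 3.07 | 40% |
| 0.05 | 1.57 | 16% |

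**The case against.** The best defence is that a journal article condenses the full plan. It names generalised linear mixed models, does not say they serve repeated measures alone, and cites cluster-trial methods for the sample size. A clinic effect may therefore stand in the full plan. That is fair for the mixed models: the clinic term is unstated, not excluded. It does not rescue the ANOVA, which is named as the between-arm test for survey scores.

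Several stronger readings are tempting, and the document does not support them:

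- That the error rate is 59% for women and 16% for providers. Both need ICC 0.05, which the article implies only for continuous outcomes, and the second also needs 20 providers per site. Table 3 itself is reproduced at ICC 0, where there is no inflation.
- That every planned analysis ignores the clinic. Fidelity is compared on site composites.
- That the 5% level is shown to fail for both primary outcomes. No model is named specifically for uptake. Adoption is a facility-level outcome drawn from logs, surveys and interviews, so the ANOVA sentence does not settle how it will be tested.
- That Tukey's procedure is the test of arm. It is offered to locate differences between sites.

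Inflation also shrinks with few respondents per site, and the sustainment survey plans only 6 to 10 providers in total.

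**Conclusion.** The point holds in qualified form. The ANOVA on individual survey scores is a wrong stated analysis for a trial that randomises clinics, and the mixed-model sentence names a dependence that does not protect the comparison of arms. Both conflict with the article's own randomisation and sample size sections, so this is more than detail left to a fuller plan.

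The size is conditional on the clinic being left out: about 11% to 59% for women-level outcomes and about 5% to 16% for provider surveys, over an assumed ICC of 0.002 to 0.05 with 240 women and 20 providers per site. The upper ends should not be quoted without those conditions. The women-level exposure is larger but rests on the less explicit text; the provider exposure is smaller but rests on text that is plain.

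**What to change.** For every between-arm comparison of women-level and survey outcomes, including those carried into the sustainment phase:

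- Replace the individual-level ANOVA with site-level summaries (covariate-adjusted where wanted) and a t test on 2 df, or with a mixed model that has a site random intercept and a 2-df small-sample reference.
- Nest participant effects for repeated measures within site.
- Report all four site values, and keep contrasts between sites as descriptive only.
- State the ICC assumed for binary and provider outcomes.

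The edit is to wording, but the cost is real. The critical value rises from 1.96 to 4.30, intervals widen greatly, and power for 15% versus 30% holds near 80% only if the ICC is close to 0. This should be reported as a limitation of having two clinics per arm. The limit comes from the design; the present wording only leaves it unseen.

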### Implementation phase

Assess the effectiveness of the HOPE 2.0 intervention and the success of the implementation plan in a hybrid type 2 trial.

*Hypothesis: Cervical screening uptake by HPVSS will be significantly higher among WLWH in the intervention vs. the control group, and implementation outcomes scores among intervention group providers will be significantly higher than those of control group providers.*

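### The survey analysis names study arm as the ANOVA factor but site as the Tukey HSD factor; site-pair tests do not address the arm hypothesis, and an arm ANOVA that does not treat site as the cluster does not hold 5%

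*Protocol article*

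**What the plan says.** The Implementation phase hypothesis on survey scores is a comparison of arms: "implementation outcomes scores among intervention group providers will be significantly higher than those of control group providers". Under Randomization, "Study sites are the unit of randomization", with "two sites in the intervention group and two sites in the control group".

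For survey items, the Quantitative data analysis section says "we will use ANOVA to determine differences in implementation outcome scores between study arms", and completes the sentence "with Tukey HSD (honestly significant difference) post hoc analysis to determine specific sites that significantly differ". The same section mentions mixed models for repeated measures on participants; it does not name site as a cluster there or in the survey sentence. Tests are two-sided at 0.05. The Sustainment phase Analysis section carries the same statistical methods forward.

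For continuous outcomes, the Sample size estimation section states: "we used estimated variance = 1 (standardized), and variance within clusters = 0.95". That implies an ICC of 0.05.

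**The concern.** Tukey HSD compares all pairs of levels of one factor. It can name sites only if that factor is the four-level site, yet the ANOVA it is meant to follow is stated on the two-level arm. One sentence therefore describes two analyses with different null hypotheses, and does not say which one answers the hypothesis.

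Of the six site pairs, two lie within an arm and carry no information about the implementation support strategies (ISS). The other four each compare one clinic with one clinic, so the ISS effect cannot be separated from the clinics' own differences. A flagged cross-arm pair could be taken as support for ISS when it shows only that two clinics differ.

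The arm half of the sentence has its own weakness. Allocation was by site, but the ANOVA as described treats respondents as independent.

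**Working it through.** **Inputs.** Four sites, two per arm (Randomization). Two-sided α = 0.05 (Statistical analysis plan). Total variance 1 and within-cluster variance 0.95 (Sample size estimation), so ICC = (1 − 0.95)/1 = 0.05. That value was set for variability among the women; applying it to providers is an assumption. Respondents per site: 20, which is the 80 providers in the Abstract divided equally over four sites (an assumption), and 240, the plan's minimum number of women per site. Scores are taken as normal and sites as equal in size. The plan gives no error rate for this analysis, so there is no stated figure to reproduce.

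**1. Pairs.** Four sites give 4×3/2 = 6 pairs: 2 within an arm and 2×2 = 4 across arms.

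**2. Tukey with exactly equal arm means.** Put the clinics in each arm at +d and −d, so that both arm means are zero. Two of the four cross-arm pairs then truly differ by 2d. Tukey flags an observed gap larger than q√(MSW/n), where MSW is the within-site mean square.
- n = 20, d = 0.25: q = 3.715, so the threshold is about 3.715/√20 = 0.83 SD, against a true gap of 0.5 SD.
- n = 240, d = 0.15: q = 3.640, so the threshold is about 3.640/√240 = 0.23 SD, against a true gap of 0.3 SD.

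Simulated rejection rates:

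| Test | n = 20, ±0.25 SD | n = 240, ±0.15 SD |
|---|---|---|
| At least one cross-arm Tukey pair | 29% | 94% |
| At least one same-arm Tukey pair | 28% | 94% |
| Two-group ANOVA on arm, as written | 4% | 5% |
| Four-group F test on site (not stated in the plan) | 42% | 98% |

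The site comparisons react to clinic differences. The arm ANOVA does not, because these offsets cancel within each arm and only enlarge its residual.

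**3. The arm ANOVA when clinic effects are random.** Real clinic effects need not cancel. With no arm effect, between-site variance 0.05 and within-site variance 0.95, the difference D between the arm averages of site means has variance 0.05 + 0.95/n. Within-site error credits it with only 0.95/n. The understatement factor is 1 + n×0.05/0.95:
- n = 20: 1 + 1.05 = 2.05
- n = 240: 1 + 12.63 = 13.63

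Simulated rejection rates with no arm effect:

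| Test | n = 20 | n = 240 |
|---|---|---|
| Two-group ANOVA on arm | 16% | 59% |
| Arm contrast with within-site error | 17% | 59–60% |
| t-test on the four site means (2 df) | 5% | 5% |

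Replacing the ANOVA by an arm contrast is therefore not enough. The error term has to come from between-site variation.

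**4. Power of the valid test.** For a true 0.6 SD arm effect at 20 per site with ICC 0, the standard error of D is √(1/20) = 0.224 and the noncentrality is 0.6/0.224 = 2.68. With 2 df the critical value is 4.30 and power is about 33%. With within-site error (76 df) the critical value is 1.99 and power is about 75%. At ICC 0.05 the standard error is √(0.05 + 0.95/20) = 0.312, the noncentrality is 1.92, and the 2-df power falls to about 21%.

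**The case against.** The strongest reply is that the plan names study arm as the ANOVA factor. A reader might infer from the Tukey clause that the ANOVA itself is a four-site test, with two of its three degrees of freedom spent on same-arm differences, rejecting 42% or 98% of the time when arm means are equal. The text does not support that as a fact. It says the ANOVA is between arms, and in those same scenarios an ANOVA run that way rejects 4–5%. The 42% and 98% belong to a test that the Tukey wording only implies. This reply stands, and it limits the point.

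It can also be said that the Tukey step is meant to describe sites, that nowhere does the plan say a site pair will count as evidence for ISS, and that mixed models in the same section offer another route to an arm comparison over time. All of that is fair. A misleading reading of a site pair is a risk left open by the wording, not a declared intention, and an exploratory label would largely meet it. It does not remove the mismatch of factors within one sentence. The mixed-model sentence speaks of repeated participant measures and not of site, so it does not supply the missing cluster term.

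**Conclusion.** The point holds in a limited form. The survey sentence uses arm for the ANOVA and site for the post hoc test; a post hoc test has no role with two arms, and site pairs cannot test the arm hypothesis. With equal arm means, a cross-arm pair is flagged in about 29% or 94% of trials in the two scenarios, whose clinic offsets are illustrative.

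The ANOVA on arm is not inflated by same-arm differences that cancel. It is inflated by clinic effects in general, because site is not its unit of error: about 16% at 20 per site and 59% at 240 per site with ICC 0.05. The first figure bears on the provider hypothesis and assumes that the women's ICC applies to providers and that the 80 providers are spread evenly; the second bears on surveys of the women. Both assume normal scores and equal site sizes. With a smaller ICC the inflation is less: at ICC 0.01 the arm ANOVA rejects about 7% at 20 per site and 29% at 240 per site.

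**What to change.** In Quantitative data analysis, replace the ANOVA and Tukey sentence with one pre-specified intervention-minus-control contrast as the test of the survey-score hypothesis. Take its error term from between-site variation: either a t-test on the four site means with 2 df, or a mixed model with a site random effect and a small-sample correction. Delete the Tukey step, or label it exploratory. Show the four site means with confidence intervals descriptively, and state that differences between individual sites are not evidence about ISS. Make the same change apply to the Sustainment phase Analysis section.

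The edit is a change of wording. Its real cost is power: with 2 df, about 33% for a 0.6 SD effect at 20 per site with ICC 0, against 75% for the contrast with within-site error, and about 21% at ICC 0.05. That loss reflects having two sites per arm; the higher figure comes from an error term that leaves out variation between clinics. The plan should say so and put weight on the estimate and its interval.

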#### Control arm

Providers and clinic managers at control sites will receive baseline training on study implementation, but will not receive any ISS or implementation plan training (Table 2). They will, however, be required to follow Steps 2, 3, and 4 described in the intervention arm described above, except for patient navigator support.

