### Outcomes measures

The primary outcomes of interest in this type 2 hybrid trial are 1) the effectiveness of the HOPE 2.0 intervention in increasing uptake of cervical screening among WLWH, and 2) the adoption of HOPE 2.0 intervention at the facility level. Other outcomes, including cost, fidelity, penetration, and sustainability, will be assessed as secondary outcomes. Additionally, Proctor et al.’s [61] client (i.e., WLWH) health outcomes will also be assessed (Fig. 2).*Cervical screening uptake* is defined as the proportion of WLWH in each study arm that successfully complete the cervical screening process. In the intervention arm, completing the process requires the WLWH to present to the clinic, collect a self-test kit, collect a cervical sample, and submit the sample to the clinic for testing. In the control arm, completing the process requires the WLWH to present to the clinic and receive a pap smear/cervical sample collection from a provider. WLWH in either study arm who do not complete the entire process will not be considered as completing uptake. Uptake assessment will therefore be determined as proportion of WLWH with complete screening out of all women enrolled in each study arm.*Program Adoption* is defined as the decision of healthcare workers (i.e., providers and management) and patients (described as patient uptake) to commit to and use HOPE 2.0 and ISS adoption. Adoption will be measured at provider, management, and patient levels using a variety of data logs, surveys, and interviews.At the management level, we will assess (i) the number of ISS training sessions attended and (ii) the degree to which ISS components are used to support providers.At the provider level, we will assess (i) the number of ISS training sessions attended, (ii) the degree to which ISS components are used, and (iii) the number of implementation plan steps followed. Additionally, we will assess providers’ (i) implementation experience (i.e., resource availability, managerial support, and technical issues confronted); and (ii) operational experience (i.e., workload increase or decrease, flow of health facility communication, and any skills needed).*Implementation Cost* is defined as the total expenses (facility/provider and patient) for implementing HOPE 2.0. Cost will be assessed at the health facility level in both study arms. We will use a micro-costing approach to estimate the economic costs associated with each study arm. The direct measure method of micro-costing involves tracking resources used and enumerating unit costs for each resource to precisely estimate cumulative costs associated with each study arm [62]. Implementation cost will be measured at the health facility level and patient level, utilizing a variety of cost-tracking databases throughout the study period to itemize, quantify, and value resources.At the health facility level, a cost-tracking database will be used throughout the study period to itemize, quantify, and value resources. Costs at the facility level include (i) number of hours staff spent on HOPE 2.0 training; (ii) sampling materials, including kits and laboratory testing costs; (iii) recruitment (i.e., time spent identifying and contacting eligible women, advertising materials, participant incentives); (iv) HOPE 2.0 delivery (with and without ISS); and (v) treatment and biopsies.Cost to the patient will include tracking of participant out-of-pocket costs (e.g., transportation, childcare, phone data, time spent on HOPE 2.0 procedures). French et al.’s outpatient cost survey [63] (5 items) will be adapted to measure patient-level costs.Note: Time effort will be estimated using the hourly wages of WLWH and healthcare workers.*Fidelity* is the degree to which HOPE 2.0 and its ISS are implemented as planned.At the provider level, utilizing surveys, log sheets, and interviews, we will assess (i) the degree of adherence to HOPE 2.0/ISS protocols (Intervention) and HOPE 2.0 (Control) during implementation, (ii) the dose of the program delivered, and (iii) the quality of program delivery.At the management level, we will assess (i) adherence to ISS protocol (Intervention only) and (ii) overall management support for providers (both arms).We will utilize log sheets and interviews, as well as observations, and the Process Evaluation Checklist (PEC) [64] throughout to track the fidelity of implementation and overall project progress.*Program Penetration* for this proposal is the integration of HOPE 2.0/ISS within the HIV subsystem of study facility settings [61]. We will assess penetration outcomes at provider and management levels by determining the proportion of personnel who actually deliver on a HOPE 2.0 program task/role, out of the number trained or expected to deliver on that task/role.At the management level, we will utilize log sheets and interviews to measure the expected tasks or roles to be evaluated, which will be (i) the provision of technical support and (ii) facilitating a conducive HOPE 2.0 implementation climate for providers.At the provider level, we will utilize log sheets and interviews to measure the expected tasks to be evaluated, which are (i) screening and recruitment of eligible WLWH, (ii) delivery of HOPE 2.0 to enrolled WLWH, and (iii) follow-up on all testing outcomes and completion of required documentation for these tasks/roles.*Program Effectiveness* is defined as the impact of the ISS on 1) providers' self-efficacy in implementing HOPE 2.0, 2) WLWH screening uptake, and 3) treatment outcome. We will assess effectiveness outcomes at management, provider, and WLWH levels utilizing surveys, log sheets, and interviews.At the management level, we will assess (i) the frequency of support that management delivers to providers, (ii) management self-efficacy in supporting HOPE 2.0 implementation, and (iii) challenges in supporting HOPE 2.0 implementation at their facilities, utilizing log sheets and interviews.At the provider level, we will assess (i) self-efficacy for implementing HOPE, (ii) fidelity of HOPE 2.0 intervention delivery, (iii) number of WLWH screened and women with positive results who are treated, and (iv) the type, frequency, duration, and quality of service provided to patients (WLWH).At the WLWH level, we will assess the impact of HOPE 2.0 on patients’ (WLWH) screening uptake (i.e., service outcome) and receipt of screening results, patient satisfaction, and for women with positive screening results, clinical follow-up, and evaluation for, and receipt of CC treatment where appropriate (i.e., client outcomes). Assessment procedures: WLWH in both study arms will complete the screening and satisfaction outcome survey within one month of completing HOPE 2.0. Within one month of screening, providers will check the lab registry and will review the electronic medical record to confirm screening completion. Treatment compliance will be evaluated within 6 months of positive result notification. The screening and treatment completion outcomes will be binary (yes/no), test results (positive, negative, or inadequate), treatment follow-up (yes, no, or lost-to-follow-up), and patient satisfaction will be measured using a patient satisfaction survey [65].

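### Fidelity covers HOPE 2.0 plus implementation support strategies in one arm and HOPE 2.0 alone in the other, yet composite site scores are compared across arms with no limit to shared items

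*Protocol article*

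**What the plan says.** All references are to the protocol article.

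- **Definition (Outcomes measures).** Fidelity "is the degree to which HOPE 2.0 and its ISS are implemented as planned", so ISS is part of the construct.
- **Provider level (Outcomes measures).** What is assessed includes "the degree of adherence to HOPE 2.0/ISS protocols (Intervention) and HOPE 2.0 (Control) during implementation". Dose and quality of delivery are also assessed.
- **Management level (Outcomes measures).** Two elements are listed: "adherence to ISS protocol (Intervention only") and "overall management support for providers (both arms").
- **Instruments (Outcomes measures).** "We will utilize log sheets and interviews, as well as observations, and the Process Evaluation Checklist (PEC") to follow fidelity throughout.
- **Control arm.** Providers and managers at control sites get baseline training "but will not receive any ISS or implementation plan training". They follow the same delivery steps as the intervention arm, apart from patient navigator support.
- **Fidelity analysis (Quantitative data analysis).** "The fidelity checklist and activity log sheets at each study site will be aggregated", and then "composite site scores will be calculated and compared across intervention and control sites". The article states no restriction to shared items and no separate ISS sub-score.

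**The concern.** The arms differ mainly in whether providers receive ISS and the implementation plan. A useful fidelity comparison would show whether that support leads to more faithful delivery of HOPE 2.0. The article wants to know this: faithful HOPE 2.0 delivery is one of its provider-level measures under Program Effectiveness, which it defines as what ISS achieves.

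If ISS adherence is also counted in the score, part of the exposure sits inside the outcome. Control sites receive no ISS, so those elements cannot apply to them. A difference between arms could then come from better HOPE 2.0 delivery, from how closely ISS was followed, or simply from a longer list of items, and the composite alone would not show which. The Implementation phase hypothesis expects higher implementation scores among intervention providers, and a raw sum would move in that direction by construction.

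**Working it through.** The article gives no numerical fidelity figure to reproduce. The check is whether two scores built as described can be compared, followed by an illustration.

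**Content by arm, from Outcomes measures**

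| Element | Intervention | Control |
|---|---|---|
| Provider adherence to HOPE 2.0 | yes | yes |
| Provider adherence to ISS | yes | no |
| Manager adherence to ISS | yes | no |
| Management support for providers | yes | yes |

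The fidelity analysis compares site composites drawn from the instruments that record these elements. Nothing in it removes the second and third rows.

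**Notation.** H is the number of HOPE 2.0 items, with adherence h equal in both arms. I is the number of ISS items, with adherence s, at intervention sites only. The true HOPE 2.0 difference is therefore zero. The difference, intervention minus control, is:

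- raw sum: (H·h + I·s) − H·h = I·s, never negative
- percentage of applicable items: (H·h + I·s)/(H + I) − h = I·(s − h)/(H + I), zero only when s = h
- common denominator with control scored zero on ISS: I·s/(H + I), never negative
- shared HOPE 2.0 items only: h − h = 0 for every H, I and s

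**Illustration.** All inputs are assumed: H = 10, h = 0.8, I = 5 or 10, s = 0.5 or 0.9.

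| I | s | Raw sum | Percentage of applicable items | Control zero on ISS |
|---|---|---|---|---|
| 5 | 0.5 | 10.5 vs 8.0 | 70.0 vs 80.0 (−10.0) | 70.0 vs 53.3 (+16.7) |
| 5 | 0.9 | 12.5 vs 8.0 | 83.3 vs 80.0 (+3.3) | 83.3 vs 53.3 (+30.0) |
| 10 | 0.5 | 13.0 vs 8.0 | 65.0 vs 80.0 (−15.0) | 65.0 vs 40.0 (+25.0) |
| 10 | 0.9 | 17.0 vs 8.0 | 85.0 vs 80.0 (+5.0) | 85.0 vs 40.0 (+45.0) |

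Over a wider assumed grid (H = 10; I = 2, 5, 10; h = 0.6, 0.8; s = 0.4 to 1.0), the raw sum differs by 0.8 to 10 points. The percentage of applicable items differs by −20 to +20 percentage points, and the common-denominator score by 6.7 to 50 percentage points. The shared-item score differs by 0 throughout.

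**When HOPE 2.0 delivery does differ.** With adherence h₁ (intervention) and h₀ (control), the percentage difference is

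[H/(H + I)]·(h₁ − h₀) + [I/(H + I)]·(s − h₀).

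The weight on HOPE 2.0 delivery is 10/15 = 67% for I = 5 and 10/20 = 50% for I = 10. The composite still responds to HOPE 2.0 delivery, but adds a second term that has nothing to do with the contrast of interest.

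**The case against.** Five points can be made on the other side.

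1. **The analysis section lists no items.** It names the checklist and activity logs, while some fidelity data also come from surveys and interviews, so ISS adherence may partly or wholly sit outside the composite. This stands as a limit on certainty: that ISS items enter the score is an inference. It is the natural one, because the definition includes ISS and the logs and checklist are the stated means of tracking fidelity.
2. **Scoring rules belong in the full protocol or analysis plan.** This is true of item lists and denominators, and their absence is no criticism. What the article does state is content that differs by arm together with a comparison across arms, and that pairing is the problem.
3. **Adherence to each arm's assigned package is a legitimate quantity.** It is, and it fits the stated definition within an arm. As a contrast between arms it cannot separate HOPE 2.0 delivery from ISS uptake.
4. **The distortion is easily overstated.** A reader might infer that the sign of the difference depends on ISS adherence and scoring rather than on HOPE 2.0 delivery. The documents do not support that: HOPE 2.0 items keep much of the weight, and dose, quality of delivery and management support in both arms would dilute the ISS share. A reader might also take from the raw-sum column a spurious gain of 31% to 113% (10.5/8.0 to 17.0/8.0). That needs raw summing, which the article never states, as well as the assumed inputs.
5. **The stakes are limited.** Outcomes measures makes fidelity secondary, although the Abstract lists it with the primary outcomes. The fidelity comparison rests on four site scores, and no test is named for it. This stands and keeps the point modest.

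**Conclusion.** The concern holds as a matter of comparability. Following the text as written, the between-arm fidelity difference combines HOPE 2.0 delivery with ISS adherence, which only intervention sites can show. With equal HOPE 2.0 delivery, a raw sum favours intervention. A percentage of applicable items shifts either way unless ISS and HOPE adherence coincide.

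The size cannot be fixed from the article. Item counts and adherence rates in the illustration are assumptions, and the conclusion also rests on ISS items entering the composite. It should be corrected, but it does not threaten the trial: under Outcomes measures fidelity is secondary, and the screening uptake comparison is not touched.

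**What to change.** - Base the between-arm fidelity comparison on HOPE 2.0 items delivered in both arms, scored as a percentage of applicable items. Leave out patient-navigator items, because the Control arm section excepts control sites from navigator support.
- Report management support for providers, which is assessed in both arms, as a separate measure.
- Report ISS adherence descriptively for intervention sites only.

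The cost is a sentence or two in the analysis plan and a tag on each checklist and log item (shared HOPE 2.0, navigator, management support or ISS). No new data are needed. If the sponsor already intends a score based on HOPE 2.0 only, stating so settles most of the point, with the navigator items still to be set aside.
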